## Abstract

**Background:**

Irritable bowel syndrome with diarrhoea (IBS-D) affects up to 4% of the general population. Symptoms include frequent, loose, or watery stools with associated urgency, resulting in marked reduction of quality of life and loss of work productivity. Ondansetron, a 5HT_3_ receptor antagonist, has had an excellent safety record for over 20 years as an antiemetic, yet is not widely used in the treatment of IBS-D. It has, however, been shown to slow colonic transit and in a small randomised, placebo-controlled, cross-over pilot study, benefited patients with IBS-D.

**Methods:**

This trial is a phase III, parallel group, randomised, double-blind, multi-centre, placebo-controlled trial, with embedded mechanistic studies. Participants (*n* = 400) meeting Rome IV criteria for IBS-D will be recruited from outpatient and primary care clinics and by social media to receive either ondansetron (dose titrated up to 24 mg daily) or placebo for 12 weeks. Throughout the trial, participants will record their worst abdominal pain, worst urgency, stool frequency, and stool consistency on a daily basis.

The primary endpoint is the proportion of “responders” in each group, using Food and Drug Administration (FDA) recommendations. Secondary endpoints include pain intensity, stool consistency, frequency, and urgency. Mood and quality of life will also be assessed.

Mechanistic assessments will include whole gut transit, faecal tryptase and faecal bile acid concentrations at baseline and between weeks 8 and 11. A subgroup of participants will also undergo assessment of sensitivity (*n* = 80) using the barostat, and/or high-resolution colonic manometry (*n* = 40) to assess motor patterns in the left colon and the impact of ondansetron.

**Discussion:**

The TRITON trial aims to assess the effect of ondansetron across multiple centres. By defining ondansetron’s mechanisms of action we hope to better identify patients with IBS-D who are likely to respond.

**Trial registration:**

ISRCTN, ISRCTN17508514, Registered on 2 October 2017.

**Electronic supplementary material:**

The online version of this article (10.1186/s13063-019-3562-6) contains supplementary material, which is available to authorized users.

## Background and rationale

Irritable bowel syndrome (IBS), which affects around 10% of the population, accounts for 1.8 million consultations per year in primary care in England and Wales. Around one third of these patients meet criteria for IBS with diarrhoea (IBS-D). Symptoms include frequent, loose, or watery stools with associated urgency, which can severely limit socialising, travelling, and eating out. This can lead to a marked reduction in quality of life and loss of work productivity. When patients with IBS are asked to rank symptoms in order of importance, erratic bowel habit is rated first, followed by abdominal pain and, for those with diarrhoea, urgency [1]. This can often be associated with incontinence, which is socially debilitating, but often under-reported [2].

Current treatments for patients with IBS-D such as loperamide reduce bowel frequency, but do not improve abdominal pain, and often lead to constipation. The lack of effective treatments results in frequent referrals to secondary care, and such patients represent a significant proportion of gastroenterology outpatients.

A previous meta-analysis [3] showed that the 5-hydroxytryptamine-3 receptor antagonists (5HT_3_RAs) alosetron and cilansetron benefited such patients, improving stool consistency, and reducing both frequency and urgency of defaecation. However, these drugs had serious side effects, including constipation in 25% of patients and, rarely, ischaemic colitis (1 in 700). Alosetron was initially withdrawn and now is available in the USA only, through risk evaluation and mitigation strategy (REMS) and is not available in Europe. Cilansetron never came to market, while ramosetron, another 5-HT3 receptor antagonist is only available in Japan where it is licensed for IBS-D, with several good-quality trials confirming its benefit [4, 5].

Ondansetron is a widely used 5HT_3_RA that, unlike alosetron, has not been associated with ischaemic colitis. A pilot randomised, placebo-controlled cross-over trial showed that 5 weeks of ondansetron was effective in improving diarrhoea and urgency [6]. Currently we do not understand exactly how it works, nor can we predict the individual dose required for optimum effect, which varies widely. One key effect we found, also seen with other 5HT_3_RAs [7], was a marked reduction in urgency, which may be important in improving quality of life in patients with IBS-D [8].

### Potential mechanisms of action of 5HT_3_ receptor antagonists

The 5HT_3_RAs slow colonic transit, an effect we found particularly marked in the left colon and the rectosigmoid region of patients with IBS-D, but the underlying mechanism was unclear [6]. Previous studies of the impact of 5HT_3_RAs on human colonic motility [9, 10] showed that the 5HT_3_RAs alosetron and cilansetron increased peri-prandial frequency of colonic contractions, and mean amplitude of contractions in the left colon. We hypothesise that 5HT_3_RAs increase retrograde sigmoid motility, perhaps enhancing “brake” function [11, 12], which would be a novel mode of action. In our pilot study we showed the decrease in urgency correlated directly with the reduction in faecal protease [13], but whether this represents a true causal relationship or just an epiphenomenon is unclear. Faecal proteases have been shown to be increased in IBS-D and, at least in animal models, cause hypersensitivity to rectal distension via activation of protease activated receptors type 2 (PAR2) [14]. We have shown that most faecal proteases are endogenous [13], representing pancreatic enzymes that have escaped degradation by colonic bacteria. We hypothesise that slowing gut transit reduces faecal protease, by allowing time for bacterial degradation, and that this may also contribute to the beneficial effects of ondansetron. This might also improve the anal soreness that is commonly reported by patients with IBS-D. Bile acids have also been shown to sensitise the rectum [15], and elevated faecal bile acids have been identified by several groups in patients with IBS-D [16]. Slowing transit may increase the time for bile acid deconjugation by colonic bacteria, and therefore enhance absorption, but how important this is in reducing rectal sensitivity, compared with the effects on faecal proteases, is unclear.

### 5HT_3_ receptor antagonist sensitivity

We have also shown that individuals vary widely in their responsiveness to ondansetron, explaining why trials using fixed doses of 5HT_3_RAs result in severe constipation in some patients. When patients were allowed to have dose titration we found that constipation was rare, occurring in only 2% of patients. However, the required dose of ondansetron ranged from 4 mg on alternate days to 8 mg three times a day (t.d.s.). The reasons for this variation are unclear but recent evidence suggests that responsiveness to 5HT_3_RAs might be linked to polymorphisms in the genes controlling 5HT synthesis. Serotonin availability in the rectal mucosa is thought to be determined by the activity of the rate-limiting synthetic enzyme tryptophan hydroxylase-1 (TPH-1), which produces serotonin in enterochromaffin cells. A recent small study showed that TPH-1 mRNA levels in rectal mucosa (and thus presumably serotonin synthesis rate) were approximately doubled in responders to another 5HT_3_RA, ramosetron, compared with non-responders, and that this was linked to the TPH-1 genotype [17]. TPH-1 rs211105 minor allele G was found in 44% of non-responders, but only in 4% of responders, indicating that possessing the major allele increases responsiveness to the drug. It was also associated with worse diarrhoea, possibly because of the greater 5HT synthesis.

### Investigational agent

Ondansetron is a potent, highly selective 5HT_3_RA, which blocks 5HT_3_ receptors in the gastro-intestinal tract and in the central nervous system. Ondansetron is currently licenced for use in adults and children for the management of nausea and vomiting induced by cytotoxic chemotherapy and radiotherapy, and for the prevention and treatment of post-operative nausea and vomiting. Constipation is an unintended side effect of ondansetron, which was first shown to slow colonic transit 30 years ago [18–20]. In our pilot study, 120 patients were recruited to a randomised double-blind, placebo-controlled, cross-over trial of ondansetron treatment for IBS-D. Patients were randomised to receive ondansetron (2 mg per day up to 8 mg t.d.s) followed by placebo or placebo followed by ondansetron. Patients began on drug A for a period of 5 weeks, then underwent a washout period of 2–3 weeks, and then commenced drug B for 5 weeks. The primary outcome measure for the study was the difference in average stool consistency in the last 2 weeks of treatment of ondansetron versus placebo, and this showed a highly significant improvement with active treatment. We also showed significant benefits for both urgency and stool frequency, with associated slowing of whole gut transit. Despite having limitations, the results of this pilot study were very encouraging, supporting our clinical experience of the benefits of ondansetron.

## Objectives

The primary objective is to determine the effectiveness and safety of ondansetron in patients with symptoms of IBS-D, including urgency, looseness of stool, frequency of defaecation, and abdominal pain. The trial also aims to understand further the mode of action of ondansetron in these patients. More specifically, we will examine the role of rectal sensitivity and compliance, faecal bile acids and proteases, post-prandial sigmoid motility, and genetic variation of serotonin synthesis, both in terms of symptom generation in IBS-D and in responsiveness to ondansetron. This will be achieved by performing mechanistic studies within the clinical trial to determine if changes in symptoms are correlated with changes in these biomarkers.

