#### Subgroup analyses

No subgroup analyses are planned.

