#### Mechanistic studies

Mechanistic studies will be analysed blinded to the intervention allocation, by the site research fellow under supervision of the Chief investigator and local supervising PIs. The differences between treatment groups in changes in whole gut transit times, colonic motility measures (percent time of cyclical retrograde contractions and high-amplitude propagating contraction (HAPC) frequency), rectal compliance, and thresholds for urgency and pain measured using the barostat, faecal bile acid concentrations, and faecal tryptase will each be assessed by linear regression models. In addition, exploratory mediator analyses will explore whether treatment effects, in terms of changes in urgency or pain, are mediated through changes in faecal bile acids or protease. Exploratory subgroup analysis (tests of interactions) will be performed to investigate the effect of the presence of each specified single nucleotide polymorphism allele on response to treatment, using logistic regression with addition of an interaction term for the allele and treatment.

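### For the non-genetic biomarkers, every analysis described uses post-randomisation change, so it can address mode of action but not which patients respond; only SNP alleles get a treatment interaction test

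*Protocol article*

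**What the plan says.** The Objectives section lists rectal sensitivity and compliance, faecal bile acids and proteases, sigmoid motility after meals, and genetic variation in serotonin synthesis. Their role is to be examined "both in terms of symptom generation in IBS-D and in responsiveness to ondansetron". The next sentence gives the means: studies within the trial that will "determine if changes in symptoms are correlated with changes in these biomarkers". The Discussion part of the abstract adds that, by defining mechanisms, "we hope to better identify patients with IBS-D who are likely to respond".

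The analyses offered are these:

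- **Mechanistic studies (Data analysis):** linear regression of "The differences between treatment groups in changes in whole gut transit times", and likewise for motility, compliance, barostat thresholds, bile acids and tryptase; exploratory mediation through change in bile acids or protease.
- **Mechanistic outcome measures:** correlation of the stool markers with change in urgency; TPH1 genotype related to mucosal 5HT and TPH-1 mRNA, final dose and responder status.
- **Mechanistic studies, genotype only:** "Exploratory subgroup analysis (tests of interactions) will be performed to investigate the effect of the presence of each specified single nucleotide polymorphism allele", "using logistic regression with addition of an interaction term for the allele and treatment".
- **Subgroup analyses:** "No subgroup analyses are planned".

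**The concern.** Whether a biomarker identifies patients who benefit from the drug is a question about its value before treatment and how the treatment effect varies with it. A change over 12 weeks is unknown when treatment is chosen, and it is itself affected by treatment. The article uses the right tool, a treatment-by-marker interaction, for SNP alleles, but for no other biomarker in the same objective.

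Two things are at stake. First, baseline transit, stool, barostat and manometry measures are obtained before treatment in consenting patients, yet nothing described uses them as effect modifiers. Second, an unadjusted correlation of change with change can mislead. A patient with a high baseline value tends to show a larger fall through regression to the mean. If high baseline also goes with more benefit, the two changes will correlate even though the biomarker's change does nothing.

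Separately, the Subgroup analyses section and the Mechanistic studies section cannot both be literally true.

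**Working it through.** **1. Sample size available.** From the Sample size section: 17% versus 32%, 90% power, two-sided 5%, 15% attrition. With pooled variance, n per arm = [1.96·√(2·0.245·0.755) + 1.2816·√(0.17·0.83 + 0.32·0.68)]² / 0.15² = 171. That is 342 in total, and 342/0.85 = 403, close to the stated 400. Evaluable patients: 400 × 0.85 = 340, or 170 per arm. The article states no power for any interaction.

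**2. Each biomarker against the analyses described.**

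| Biomarker | Difference in change | Correlation or mediation | Baseline × treatment |
|---|---|---|---|
| Whole gut transit | yes | change correlation (Objectives, general) | no |
| Bile acids, tryptase/protease | yes | both | no |
| Barostat, manometry | yes | change correlation (Objectives, general) | no |
| Mucosal TPH-1 mRNA | no | with genotype | no |
| SNP alleles | not applicable (does not change) | with dose and responder status | yes |

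**3. Does change-change correlation reveal a predictor?** Simulation: N = 400, 2000 runs, assumed effects. The biomarker change drives the symptom change, and a baseline marker either does or does not modify the drug's effect on that change.

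- No modification: correlation 0.46 pooled, 0.44 in the active arm; the interaction test rejects in 5.0%.
- Strong modification: correlation 0.49 and 0.50; the interaction test rejects in 75%.

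The correlation hardly moves, so it does not separate the two situations.

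**4. Can it signal without any mechanism?** Assumed model, in SD units: symptom change = z(−0.5 − 0.35·B0) + e; follow-up biomarker = ρ·B0 + noise − 0.5z, where z is treatment and B0 the baseline value. Biomarker change has no causal role. In the active arm the expected correlation is 0.35(1 − ρ) / [√(2 − 2ρ) · √(1 + 0.35²)]:

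- ρ = 0.8: 0.07/(0.632 × 1.059) = 0.10
- ρ = 0.4: 0.21/(1.095 × 1.059) = 0.18

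With 170 patients, Fisher's z gives power of about 27% and 66%. Simulation (3000 trials) gives about 29% and 65%; repeat runs put the lower figure between 26% and 29%. With adjustment for baseline biomarker the rate is about 5%, the nominal level. Using both arms, adjusted for treatment only, it is 15% to 41%.

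**5. Power of the interaction test in the same model.** SE = 1/√(n·0.25).

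- n = 340: SE 0.108; 0.35/0.108 gives about 90% by formula and about 88% in simulation.
- n = 240 (assumed lower consent): SE 0.129, power about 77%.
- Detectable with 80% power at n = 340: 2.80 × 0.108 = 0.30 SD per SD.
- Responder endpoint: SE = √(1/(170·0.17·0.83) + 1/(170·0.32·0.68)) = 0.262, so a detectable interaction odds ratio of exp(2.80 × 0.262) ≈ 2.1 per SD.

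**6. Subsets.** Assumed binary marker, 50% prevalence, 17% on placebo in both strata, 32% average on active:

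| Active rates by stratum | N = 400 | N = 340 | N = 80 | N = 40 |
|---|---|---|---|---|
| 47% vs 17% (all benefit in one stratum) | 83% | 77% | 26% | 15% |
| 40% vs 24% | 33% | 29% | 10% | 7% |

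**The case against.** The strongest reply is that responsiveness can mean the pathway through which response occurs. The background hypotheses on motility, protease and bile acids are mechanistic, and for those, changes and mediation are apt. The predictive test sits on genotype, where the background section gives a prior reason to expect prediction. This is a fair reading, and it is why limiting the aim is an acceptable alternative. But the Objectives separate symptom generation from responsiveness and name one method for both, so as written the aim is wider than the method.

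A reader might infer that the trial cannot say at all who is likely to respond. The documents do not support that: the allele-by-treatment interaction is a valid exploratory test of differential response, and genotype is also related to final dose and responder status. Nor is identifying responders a formal objective; the abstract words it as a hope.

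A reader might also infer that the plan will pass off a predictor as a mediator. That is not established. The article does not say the correlations are unadjusted or confined to the active arm. It plans between-arm comparisons and mediation as well, and its background section already asks whether the urgency-protease link is causal. The Endpoint analysis section adjusts for baseline values where applicable, though whether this reaches the mechanistic models is not stated. With that adjustment the artefact disappears.

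Finally, extra exploratory models are often left to the analysis plan. That would dispose of a mere omission, but here the article positively names a method for the aim.

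**Conclusion.** The point holds for the non-genetic biomarkers. The analyses described for them can inform mode of action and cannot show which patients respond, while the data needed for the second question are already being collected. The limitation lies in the described analysis, not in the design.

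The figures are illustrative. Effect modification of 0.35 SD per SD, the 0.5 SD mean effects and the baseline-follow-up correlations of 0.4 to 0.8 are assumptions, not taken from the documents. The 29% to 65% rate of misleading signals applies only to an unadjusted active-arm correlation. Interaction tests are reasonable for markers measured in most patients (about 77% to 88% power under these assumptions), but weak in the subsets of 80 and 40.

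The conflict between the Subgroup analyses and Mechanistic studies sections is literal and needs one line to resolve. Nothing here affects the primary result; this is a worthwhile, inexpensive improvement.

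**What to change.** 1. In Mechanistic studies, add exploratory treatment-by-baseline interactions, with the biomarker continuous, for whole gut transit, faecal bile acids and faecal tryptase in all consenting patients. If subset markers are included (barostat measures, mucosal TPH-1 mRNA, n = 80), label them as low power. Alternatively, restrict the Objectives for the non-genetic biomarkers to mode of action.
2. State that the change-change associations in Objectives and Mechanistic outcome measures are adjusted for treatment and baseline biomarker value.
3. Reword Subgroup analyses so that it excepts the exploratory interactions set out under Mechanistic studies.

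No new data are needed. The cost is some wording, a few more models, and a larger number of exploratory tests that must be reported as such.

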### Trial design

TRITON is a multi-site, parallel group, randomised, double-blind, placebo-controlled trial with embedded mechanistic studies within selected sites. Our aim is to determine the superiority of ondansetron compared with placebo. In total, 400 patients with IBS-D will be randomised 1:1 to receive either ondansetron or placebo. Both treatments will be administered in oral doses of between 4 mg every third day and 24 mg daily for 12 weeks. Dose titration will be undertaken in the first 2 weeks of the trial to avoid constipation, which at a standard dose occurs in one quarter of patients. The primary outcome will be assessed over the 12 weeks post randomisation. Secondary and safety outcomes will be measured up to 16 weeks following randomisation. See Fig. 1 for an overview of the trial procedures. The Standard Protocol Items: Recommendations for Interventional Trials (SPIRIT) checklist is provided as an Additional file 1.

**Fig. 1 Fig1:**
[figure not shown]
Schedule of enrolment, interventions and assessments throughout the TRITON study. ^1^ Date of birth, National Health Service (NHS) number, address, telephone number (if consented to text messages), smoking history, height, weight. ^2^ White blood cell count (WBC), full blood count (FBC), liver function tests (LFTs), urea and electrolytes (UEs), C-reactive protein (CRP). ^3^ Titrated to optimum dose during the first 2 weeks. ^4^ Recording worst abdominal pain (0–100), worst urgency (0–100), number of investigational medicinal product (IMP) taken, use of loperamide, stool consistency of each stool passed, and relief from irritable bowel syndrome (IBS) symptoms at the end of each week. ^5^ Asking if they have passed a stool type 6 or 7, and what their worst abdominal pain score was that day. ^6^ At baseline only, Physical Symptoms Questionnaire (PHQ)-12; at baseline and visits, IBS Severity Scoring System (IBS-SSS), Short-form Leeds Dyspepsia Questionnaire (SF-LDQ), Hospital Anxiety and Depression Scale (HADS), and IBS Quality of Life Questionnaire (IBS-QOL). ^7^ Six high-rectal biopsies taken either during mechanistic assessment or at visit 3. ^8^ Whole blood (5 ml) at visit 3; serum (5 ml) at visits 3 and 5. ^9^ Four aliquots obtained and frozen at home prior to visit. ^10^ Performed at University of Nottingham & QMUL only (*n* = 40); patients will receive additional payment for participation. ^11^ Performed at Nottingham/Leeds/QMUL/UCL only (*n* = 80); patients will receive additional payment for participation

## Methods

### Trial setting

This trial will be performed initially at 18 sites in the UK. All sites will be required to recruit patients, perform all necessary protocol assessments, and offer patients the opportunity to take part in the whole-gut transit assessment and the blood and stool collection. In addition, four of the sites will perform the mechanistic assessments for the trial. Patients at all sites will be offered an opportunity to take part in the mechanistic studies but will be required to travel to one of the specified sites for these assessments.

### Eligibility criteria

#### Inclusion criteria

Patients must fulfil all of the following criteria:
Meet Rome IV criteria for IBS-D (see Table 1)Age ≥ 18 yearsHave completed standardised workup to exclude
Microscopic colitis (colonoscopy or flexible sigmoidoscopy with colonic biopsies)Bile acid diarrhoea (selenium homocholic acid taurine (SeHCAT) > 10%, C4 < 19 ng/ml or failed to respond to 1 week trial of a bile acid binding agent (colestyramine 4 g t.d.s., colesevelam 625 mg t.d.s. or equivalent))Lactose malabsorption (suggested but not mandated negative lactose breath hydrogen test, negative clinical challenge or failure to respond to lactose-free diet)Coeliac disease (confirmed by tissue transglutaminase (tTG) or duodenal biopsy)Patients of childbearing potential or with partners of childbearing potential must agree to use methods of medically acceptable forms of contraception during the trial and for 90 days after completion of trial medicationWomen of childbearing potential must test negative for pregnancy within 72 h of confirmation of eligibilityWeekly average worst pain score ≥ 30 on a 0–100-point scaleStools with a consistency of 6 or 7 on the Bristol Stool Form Score (BSFS) for 2 or more days per week

**Table 1 Tab1:** Rome IV diagnostic criteria for irritable bowel syndrome with diarrhoea

Meet Rome IV criteria for IBS-D for the past 3 months:	
- Recurrent abdominal pain at least weekly	
- Pain is associated with two or more of the following; related to defaecation, associated with a change in frequency of stool, associated with a change in form of stool	
- Symptoms onset at least 6 months prior to diagnosis	
- Abnormal stools are loose (BSFS 6 or 7) in > 25% of cases but are hard (BSFS 1 or 2) in < 25% of cases	

